Large-scale clinical trials in the West on ESA treatment of CKD patients with renal anemia include the CHOIR trial, which used epoetin alfa and set deaths and cardiovascular disease (CVD) events at the treatment target Hb concentration from 2006 to 2009 as the outcome, and the TREAT trial, which used darbepoetin alfa. These trials initially reported that groups of CKD patients whose target Hb concentrations were set close to the reference values for healthy adults using ESA ( $> 13.0$  g/dL) had a high CVD incidence rate, and that Hb concentration normalization conversely increased the risk of CVD onset. However, subsequent sub-analysis showed that the prognosis of patients who achieved the target Hb concentration regardless of the magnitude of target Hb concentration settings was favorable. Furthermore, the TREAT sub-analysis was conducted in 2010^10, which defined patients in the lower quartile of the Hb concentration change rate as the poor response group and all other patients as the favorable response group and conducted a comparative analysis of the two groups, and it showed that the poor ESA response group attained a lower average Hb concentration than the favorable response group, regardless of the higher ESA administered dose, and furthermore, that the poor ESA response group had a higher composite CVD endpoint occurrence rate and mortality rate than the favorable response group or placebo group. In other words, these results suggest that setting a high target Hb concentration itself is not the issue, but that the prognosis of patients with low ESA response is poor, or that the high ESA doses administered regardless of poor ESA response may have a negative impact. The above results indicate the importance of investigating not only the target Hb concentration but also the ESA response when conducting ESA treatment of CKD patients. However, whether background factors present in patients with a low ESA response increases the risk of CVD events or whether the administration of high concentrations of ESA is a problem is still debated, and further verification tests are needed. All large-scale clinical trial evidence on low ESA response and prognosis is based on Westerners, and there are no reports of large-scale evidence among Japanese people. It is assumed that the background factors and treatment conditions of CKD patients differ between the West and Japan. Therefore, investigating the actual conditions of low ESA response among Japanese patients with CKD is important in investigating future treatment policies for patients with low ESA response.

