## 8.2 Discontinuation criteria for each patient and its handling

The necessary items are recorded up to the traceable time point in the case report form and the “discontinuation report form” in the following patients.

- 1) When a patient has died.
- 2) When a patient cannot be contacted and becomes untraceable.

However, if the transfer destination is known, the patient will be tracked by obtaining data from the transfer destination facility or by calling, and tracing will be continued.

- 3) When a patient requests discontinuation from research participation (patient information prior to discontinuation can be used).
- 4) When a patient has requested consent withdrawal (patient information after registration cannot be used).

- 5) When the lead principal physician or study physician deemed that research participation should be discontinued.

Patients in whom any of the following are applicable are not considered discontinued, with normal observation period inspections continued to the extent possible, and information up to the time point of 96 weeks collected.

- 1) Patients who transitioned to renal replacement therapy (dialysis, kidney transplantation).
- 2) When a patient has requested discontinuation of darbepoetin alfa use.
- 3) When the lead principal physician or study physician deemed that darbepoetin alfa use should be discontinued due to adverse events, etc.

The lead principal physician or study physician will make efforts to provide the best possible treatment to the patient even after discontinuation of research participation.

If it was determined after registration that a patient did not meet the eligibility criteria at the time of registration, then this will be considered “ineligible after registration,” and research participation will be concluded for the patient. Adverse event information up to 30 days after the decision to complete participation will be reported for patients in whom darbepoetin alfa was administered even once.

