|------------------------------|-----------------------------------------------------------------------------------------------------------------------------------------------------------------------------------------------------------------------------------------------------------------------------------------------------------------------------------------------------------------------------------------------------------------------------------------------------------------------------------------------------------------------------------------------------------------------------------------------------------------------------------------------------------------------------------------------------------------------------------------------------------------------------------------------------------------------------------------------------------------------------------------------------------------------------------------------------------------------------------------------------------------------------------------------------------------------------------------------------------------------------------------------------|
| Renal function deterioration | 
① Initiation of maintenance dialysis, ② kidney transplantation, ③ 50% decrease in eGFR, ④ eGFR less than or equal to 6mL/min/1.73 m^2
 
< Supplement >
The eGFR decline rate is calculated with the average eGFR value from the start of treatment to up to 12 weeks as the baseline.
 
The first point where decreases are observed at three consecutive points is used for ③ 50% decrease in eGFR and ④ eGFR less than or equal to 6mL/min/1.73 m^2
                                                                                                                                                                                                                                                                                                                                                                                                                                                                                                                                                                                                                                                |

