| CVD event                    | 
Fatal
 
① Death due to myocardial infarction, ② sudden death, ③ death due to congestive heart failure, ④ death due to arrhythmia, ⑤ cerebrovascular death, ⑥ death due to aortic dissection, ⑦ death due to ischemia of major organs other than the heart / brain, ⑧ other forms of cardiovascular disease
 
Non-fatal
 
① Myocardial infarction*1, ② hospitalization due to angina pectoris, ③ hospitalization for ischemic heart disease requiring invasive intervention treatment, ④ hospitalization for congestive heart failure with chronic organic heart disease*2 (excluding arrhythmia), ⑤ hospitalization for severe arrhythmia and atrial fibrillation / atrial flutter, ⑥ hospitalization due to cerebrovascular disease, ⑦ hospitalization due to chronic arteriosclerosis obliterans, ⑧ hospitalization due to aortic dissection, ⑨ hospitalization due to ischemia of major organs other than the heart / brain
 
*1: New-onset (asymptomatic) myocardial infarction is treated as an event even without hospitalization.
*2: Includes old myocardial infarction, valvular disease, epicarditis, etc.
 |

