## 12. Definition of endpoints

### 12.1 Primary endpoints

#### 12.1.1 Renal function deterioration

Composite events of each event occurring 12 weeks after the start of treatment (see “10.4.1 Event – Renal function deterioration”) are set as renal function deterioration. The number of days until occurrence is calculated, with 12 weeks after the start of treatment as the starting point.

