### 13.3.1 Renal function deterioration, CVD event investigation

A proportional hazards model that includes the following covariates is applied, and the factors that affect event occurrence are investigated. Covariates are added or decreased as required for the investigation of the model. Hb concentration values at each measurement time point up to 24 weeks instead of week 12 of administration are also investigated. The presence of diabetic complications, arteriosclerosis, and chronic inflammation should also be considered as stratification factors. These analyses are used to investigate the prediction equation for event occurrence from the covariates.

- Age; sex; weight; eGFR, serum albumin, hemoglobin concentration, high-sensitive CRP, NT-pro BNP, folic acid, vitamin B12, serum iron, serum ferritin, and TSAT 12 weeks after the start of treatment; the presence of diabetic complications, arteriosclerosis, chronic inflammation, malignant tumor complications, hemorrhagic lesion complications, collagen disease and rheumatic disease complications, concomitant immunosuppressant or steroid use, and other myelosuppressive factors; and the darbepoetin alfa administered dose (total administered dose, administered dose 12 weeks after the start of treatment).

Next, the cut-off values of each ERI are gradually increased from the minimum value to the maximum

value; a time-dependent ROC curve of the survival time data with censoring is created, and the AUC is compared. If the cut-off value is set from the ROC curves of each obtained ERI, then these are divided into two groups at the cut-off value, Kaplan-Meier plots are created, and the annual event occurrence rate (human-year method) and 95% confidence intervals are estimated. The cut-off values of the ERIs may also be investigated using the cross-validation method, if considered useful.

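### The planned Kaplan-Meier curves by ERI group leave no place for competing death, so they overstate absolute risk, mainly for the renal endpoint

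*Protocol*

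**What the plan says.** Section 13.3.1 selects a cut-off for each ERI by ROC analysis: "a time-dependent ROC curve of the survival time data with censoring is created, and the AUC is compared". Patients are then divided at that cut-off, and "Kaplan-Meier plots are created, and the annual event occurrence rate (human-year method) and 95% confidence intervals are estimated". The section names no competing-event method.

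The two endpoints treat death differently (section 10.4.1):

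- The renal composite begins "① Initiation of maintenance dialysis, ② kidney transplantation, ③ 50% decrease in eGFR" and adds a low eGFR threshold. It contains no death.
- The fatal part of the CVD composite begins "① Death due to myocardial infarction, ② sudden death, ③ death due to congestive heart failure" and continues through other cardiovascular deaths. Death from a non-cardiovascular cause is not included.

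Section 12.1.1 defines the renal endpoint as "Composite events of each event occurring 12 weeks after the start of treatment" and counts time from week 12; section 12.1.2 does the same for CVD. Section 8.2 lists "When a patient has died" as a reason for discontinuation, with data recorded as far as the patient could be traced. By contrast, "Patients who transitioned to renal replacement therapy (dialysis, kidney transplantation" are not discontinued and stay under observation.

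On mortality by response, section 2 reports from a sub-analysis of an earlier trial that "the poor ESA response group had a higher composite CVD endpoint occurrence rate and mortality rate" than the comparison groups. It gives no figures.

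**The concern.** A patient who dies without a renal event cannot have one later. The same holds for a patient who dies of a non-cardiovascular cause without a CVD event. Kaplan-Meier distinguishes only events from censored observations. Unless such a death is counted as an event, which would change the endpoint, it is handled as if the patient remained at risk and could still have the event after the last observation. The resulting curve describes risk in a population where competing death does not occur. It lies above the proportion of patients who actually have the event.

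Section 2 gives proposing cut-off values for Japanese practice as an aim, and section 13.3.1 seeks a prediction equation for events. For that use, the absolute risk on each side of the cut-off matters, and the plots are where it is displayed. If competing mortality also differs between the ERI groups, the displayed gap is affected as well as the level. The time-dependent ROC rests on the same kind of data, so a standard estimator would censor the same deaths. The protocol names no estimator, and the effect on the AUC is not quantified here.

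**Working it through.** **The protocol's own figure.** The protocol states no Kaplan-Meier or cumulative-incidence value. Its only related figure is the event count in section 13.1, from 13.1 events per 100 person-years, 2,000 patients and two years:

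- Expected events = 2,000 × 2 × 0.131 = 524.
- Poisson 95% interval = 524 ± 1.96 × √524 = 479 to 569, in agreement with the stated 480–568.

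The rate therefore means what it appears to mean and can serve as an input. One caution is that the renal endpoint of the source trial counted death and this study's does not, so 13.1 is only a working value for the renal composite here.

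**Inputs.**

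- From the protocol: overall event rate 13.1 per 100 person-years (section 13.1); time origin at week 12, hence 84 weeks to week 96, or 588/365.25 = 1.61 years (sections 12.1 and 8.1).
- Assumed: 25% of patients in the high-ERI group, an event hazard ratio of 2, constant hazards, and the competing death rates in the table.

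**Event hazards.** With low-group hazard a, 0.75a + 0.25 × 2a = 1.25a = 0.131. This gives a = 0.1048 (low) and 0.2096 (high) per year.

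**Formulas,** for event hazard λ, competing-death hazard μ and time t:

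- Kaplan-Meier risk = 1 − exp(−λt)
- Cumulative incidence = λ/(λ+μ) × [1 − exp(−(λ+μ)t)]

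**Kaplan-Meier risk at 84 weeks.**

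- Low: 1 − exp(−0.1048 × 1.61) = 15.5%.
- High: 1 − exp(−0.2096 × 1.61) = 28.6%.
- Gap 13.1 points; risk ratio 1.84.

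**Cumulative incidence at 84 weeks.**

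| Competing deaths per 100 person-years (low vs high ERI) | Low | High | Gap (points) | Kaplan-Meier overstatement, low / high (points) |
|---|---|---|---|---|
| 2 vs 4 | 15.3% | 27.8% | 12.5 | 0.2 / 0.9 |
| 3 vs 6 | 15.2% | 27.4% | 12.2 | 0.4 / 1.3 |
| 5 vs 10 | 14.9% | 26.6% | 11.6 | 0.6 / 2.1 |
| 5 vs 15 | 14.9% | 25.6% | 10.7 | 0.6 / 3.0 |
| 3 vs 3 | 15.2% | 28.0% | 12.8 | 0.4 / 0.6 |
| 6 vs 3 | 14.8% | 28.0% | 13.2 | 0.7 / 0.6 |

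Three things follow:

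1. Kaplan-Meier is too high in both groups in every row. That part does not depend on which group dies more.
2. With higher mortality in the high-ERI group (first four rows), the gap is inflated by 13.1 − 12.5 = 0.6 points up to 13.1 − 10.7 = 2.4 points. The risk ratio moves less: from 1.84 to 1.78 with 5 vs 10.
3. With equal mortality the gap changes by about 0.3 points and the risk ratio hardly at all (1.84 vs 1.85). With lower mortality in the high-ERI group the gap is not inflated (13.1 vs 13.2).

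**Longer follow-up.** Patients enrolled early are followed past week 96 to the simultaneous outcome survey (section 10.1.4), and the discrepancy grows with time. At two years from the landmark with 5 vs 10, Kaplan-Meier gives a gap of 15.3 points and cumulative incidence 13.2.

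**The case against.** The protocol nowhere says in words that deaths are censored, and section 13.3 leaves analysis detail not recorded in the protocol to a SAP that is not at hand. That SAP may add a cumulative-incidence display. This limits the point but does not remove it. Kaplan-Meier is itself recorded in section 13.3.1, so it is a stated choice, and with these composites the method has nowhere else to put the deaths.

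A reader might infer that the curves must overstate risk most in the high-ERI group and must exaggerate the separation at the cut-off. The document does not support that as an unconditional statement. Its only evidence is the sub-analysis cited in section 2. That study grouped patients by the lower quartile of haemoglobin change and not by a dose-based index at an ROC cut-off, it was done in Western patients, and it is reported without mortality figures. The direction depends on mortality by ERI group in this cohort, and the last two table rows show the inflation shrinking or disappearing.

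Three further objections stand:

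- The CVD part is weaker. Fatal CVD is already an event, only non-cardiovascular death competes, and section 2 does not report that separately.
- The effect is modest. With 500 and 1,500 patients in the two groups (25% of 2,000, assumed, ignoring losses), the 95% half-width on the gap is about 4 points, so the shift lies within sampling error. Bias does not average out as sampling error does, but it will not dominate the picture.
- The Kaplan-Meier plots come after the cut-off is set, so they cannot influence its choice. The person-year rates in the same sentence and the proportional hazards model are sound cause-specific measures, and the analysis is declared exploratory.

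**Conclusion.** The point holds as a minor one. The planned curves overstate absolute risk in both ERI groups: clearly for the renal composite, which omits death altogether, and less for CVD, where only non-cardiovascular death competes. Whether the gap between groups is also inflated depends on mortality by ERI group, which the protocol does not quantify. If mortality is higher in the high-ERI group, as section 2 suggests for poor responders, the inflation is about 0.6 to 2.4 points on a gap of about 13 at 84 weeks. That range rests on constant hazards, a hazard ratio of 2, a 25% high-ERI share and competing death rates from 2 vs 4 to 5 vs 15 per 100 person-years. With equal or lower mortality in that group the gap is little changed.

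**What to change.** In section 13.3.1:

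- State how death before a renal event, and non-CVD death before a CVD event, are treated.
- Present Aalen-Johansen cumulative incidence curves for the ERI groups in place of Kaplan-Meier, or at least beside it, with those deaths as the competing event.
- Specify a time-dependent ROC estimator that handles competing events.
- Keep the proportional hazards model, read as cause-specific, and the person-year rates with confidence intervals.

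No new data are needed: sections 10.1.3 to 10.1.5 already collect the date of death and whether the cause was a fatal CVD event or other. The methods are in standard software. The cost is a little more analysis work and slightly lower reported absolute risks.

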### 13.3.2 eGFR decline rate

A linear mixed model, including the covariates shown in the previous sections, is applied to all the eGFR values from the start of administration to the final eGFR observation time point in order to search for factors that affect eGFR decline.

### 13.3.3 Safety evaluation

The number of occurrences is tabulated for all adverse events and adverse drug reactions. The tabulation of frequency according to content is performed according to the system organ class (SOC) and preferred term (PT) of MedDRA/J.

### 13.4 Intermediate analysis / intermediate tabulation

No intermediate analyses are conducted in this research.

Intermediate tabulations for regular reports (e.g., patient background, patient registration status, and case report collection status) are conducted in this research.

## 14. Input and submission of case report form

### 14.1 Form and submission deadline

The case report form of this research and its submission deadlines are as follows.

| Case report form title                                                                                                                                                                                                                                                                 | Submission deadline                                                                  |
|----------------------------------------------------------------------------------------------------------------------------------------------------------------------------------------------------------------------------------------------------------------------------------------|--------------------------------------------------------------------------------------|
| At the time of registration                                                                                                                                                                                                                                                            | Within four weeks after registration, up until the start of treatment                |
| Prior to the start of treatment                                                                                                                                                                                                                                                        | Within four weeks after the end of inspections at the start of treatment             |
| At the start of treatment
Two weeks after the start of treatment
Four weeks after the start of treatment
Six weeks after the start of treatment
Eight weeks after the start of treatment
10 weeks after the start of treatment
12 weeks after the start of treatment | Within four weeks after the end of inspections 12 weeks after the start of treatment |
| 16 weeks after the start of treatment                                                                                                                                                                                                                                                  | Within four weeks after the end of inspections 16 weeks after the start of treatment |

|                                                                                                 |                                                                                                                                                |
|-------------------------------------------------------------------------------------------------|------------------------------------------------------------------------------------------------------------------------------------------------|
| 24 weeks after the start of treatment                                                           | Within four weeks after the end of inspections 24 weeks after the start of treatment                                                           |
| 36 weeks after the start of treatment
48 weeks after the start of treatment                  | Within four weeks after the end of inspections 48 weeks after the start of treatment                                                           |
| 60 weeks after the start of treatment
72 weeks after the start of treatment                  | Within four weeks after the end of inspections 72 weeks after the start of treatment                                                           |
| 84 weeks after the start of treatment
96 weeks after the start of treatment                  | Within four weeks after the end of inspections 96 weeks after the start of treatment                                                           |
| Darbepoetin alfa administration status
Iron formulation details
Blood transfusion details | Submitted according to the submission time of each period                                                                                      |
| Fatal event
Non-fatal event
Renal function deterioration event
Adverse event           | Submitted according to the submission time of each period
(final outcome is within four weeks after the end of simultaneous outcome survey) |
| Discontinuation of research participation                                                       | Within four weeks after the confirmation of discontinuation / consent withdrawal (only for applicable patients)                                |

